#### Data Management

Data will be collected and handled according to the Data Management Plan that has been drafted for this project on the Data Management Plan online portal [53] and approved by ZonMw (ie, the grant provider). The progress of this study will be described in an annual report to the Medical Research Ethics Committee of Zuyderland Hospital and Zuyd University of Applied Sciences (in Dutch: *medisch-ethische toetsingscommissie van Zuyderland en Zuyd Hogeschool* [METC Z]) and the grant provider. Data will be password-protected and stored on hard disks on systems equipped with power-failure backup devices and automatic backup systems. All data will be kept confidential and anonymous. Each participant will be given a unique respondent number, not linked to a name or personal details, under which the data will be stored. Only researchers working on this project will have access to the data.

#### Potential Benefits and Risks

There are no risks or adverse effects associated with the trial. The participants in the intervention group can decide for themselves if, when, and how often they use the intervention. In addition, all the participants (intervention and control) can withdraw from this study at any time. It is expected that the use of the intervention will contribute to a healthier lifestyle, improve self-management, and have a positive impact on participants’ QoL. During this study, the control group will only participate in the online self-report questionnaires and blood pressure measurements at the GPC. They will not be denied medical care and will be able to seek additional professional support if they wish to do so. Insurance was not compulsory for this trial, as assessed by the medical ethics committee.

### Ethical Considerations

This study was approved by the METC Z before patient enrollment (NL806166.096.21, version 4.0; April 25, 2023). Informed consent (Multimedia Appendix 1) will be obtained from all the participants or legal guardians for this study. All patients will be required to provide written informed consent to participate. Participation can be discontinued at the request of the participants. Participants will receive a €10,- (10,31 USD) book voucher after completing the study. Modifications to this study protocol will be communicated to the METC Z through amendments. The METC Z has revised the informed consent materials to be given to participants and adapted them to accord with the Medical Research Involving Subjects Act. The protocol was amended to version 6.0 as of April 2023. This study conforms to the Declaration of Helsinki and is registered with the ISRCTN (International Standard Randomised Controlled Trial Number; ISRCTN12451453; registration date: December 15, 2021; last edited: September 12, 2023). All data will be kept confidential and anonymous.

## Results

This study was funded in July 2020. Data collection started in August 2022 and is likely to be completed by April 2025. As of December 2024, this study is still ongoing. Data analysis is estimated to start in the spring of 2025. A total of 127 participants have been recruited across 26 GPCs in the Netherlands. The first results are expected to be published in 2026.

## Discussion

### Overview

This study protocol describes an RCT to evaluate the effects on self-reported lifestyle behavior, psychosocial well-being, (health-related) QoL, medical consumption, and productivity costs of the blended CAG intervention integrated into general practice.

### Principal Findings

#### Overview

Previous research has investigated the effectiveness of the CAG in an online-only format [8-11]. This research found effects on PA, diet, fatigue, depression, and QoL, suggesting that the CAG is an appropriate eHealth intervention to support cancer survivorship. If similar results are found in this study, this would confirm that the online-only intervention has been appropriately adapted to the blended care context, maintaining its effectiveness. It would also suggest that the CAG could be integrated into the GPC workflow to facilitate the integration of cancer aftercare into general practice, as was proposed by the Dutch College of General Practitioners [20].

#### Comparison to Prior Work

Delivering the CAG in a blended care format improves the personalization of the care provided. This may strengthen the intervention and allow it to be better tailored to the individual recipient. Moreover, the integration of eHealth in general practice to facilitate cancer aftercare may address barriers to the uptake of cancer aftercare by general practice, as previously identified by Duineveld et al [54]. These barriers consisted of time constraints and a lack of expertise in cancer survivorship. Both of these can be complemented by effective eHealth tools such as the CAG.

### Strengths and Limitations

#### Overview

This paper describes the study protocol for an RCT of the effectiveness of a blended care intervention for cancer aftercare in general practice. Conducting an RCT strengthens our interpretation of the results by controlling for confounding through randomization. In addition, the current research is very similar to the previous research evaluating the effectiveness of the online-only CAG intervention, which allows the results to be compared and the added value of blended care to be identified. The blended care format is being added to increase the reach of our intervention, specifically targeting a population that would not access an online-only intervention on their own. The blended care protocol has been developed in cocreation with survivors, GPs, and PNs to ensure the best fit with the general practice context and the needs of survivors ([name], unpublished data, 2025). However, some challenges cannot be foreseen. Conducting the RCT in a period following the global COVID-19 pandemic may place limitations on our study protocol. For example, it may be difficult to achieve our target sample size due to recruitment problems with both GPCs and survivors of cancer. In the aftermath of COVID-19, the health care sector is facing a workforce shortage, partly due to the retirement of a large proportion of the working population [55,56]. In primary care, this is leading to the closure of GPCs as owners are not being replaced by a new generation. Meanwhile, the COVID-19 pandemic has resulted in a high rate of delayed care, further increasing the demand for GPCs and leaving little room for trial participation and research activities such as patient recruitment. This resulted in a difference in the number of GPCs recruited compared to our target. We aimed to recruit 40 GPCs, but in reality, only 26 GPCs were recruited.

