**Methods:**

A parallel-group design will compare an intervention group with a waiting list control group. Participants will be nested within GPCs and randomization will occur at the GPC level. The participants in the intervention group will receive a blended care intervention. In contrast, the participants in the waiting list control group will receive care as usual for the duration of this study and will receive the online intervention afterward. All participants will be asked to complete an online questionnaire at baseline, 6 months, and 12 months after baseline, measuring self-reported adherence to lifestyle recommendations, psychosocial well-being, and quality of life. A process evaluation and cost evaluation are also included in this study. The effects will be evaluated based on differences in residual change scores between intervention and control group participants, using multilevel linear regression analyses. Moreover, effect analyses will be supplemented with Bayes factor analyses. Finally, an economic evaluation will be conducted from a societal perspective and will include medical costs, productivity costs, and costs of the blended care intervention.

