#### Intervention Procedure

Participants in the intervention group will receive the CAG blended care intervention. This means that after completing the baseline measurement, they will be given access to the online CAG. Participants will use the online CAG program independently at home. In addition, they will be invited to 2 consultations with their GP or PN. Within the online CAG, the intervention group participants will receive personalized advice on 8 topics related to cancer survivorship based on their results at baseline. This is represented by the MRA. Participants are asked to share their MRA results with the GP or PN at their first consultation. During the first consultation, the GP or PN and the participant will discuss the MRA results. Through shared decision-making, the GP or PN will motivate the participant to choose at least 1 of the 8 subtopics to focus on for the next 4 to 6 weeks, after which the follow-up consultation will take place. During the follow-up consultation, the GP or PN will enquire about the participant’s progress with the chosen topic or topics. Any questions or problems the participant may have in interpreting the (lifestyle) advice given by the program will be addressed in the personal consultation. After the follow-up consultation, the participant will retain access to the online CAG intervention for up to 6 months after the start of the baseline measurement.

After completing the baseline measurement, participants in the control group are directed to a message thanking them for completing the questionnaire, asking them to log out and return only for the next measurement. Per GP care, participants in the control group will receive care as usual, which is mostly initiated by patient request and is usually complaint-driven. At the end of this study, the researchers will actively inform and encourage control group participants to finally use the online CAG intervention. Study groups will have full access to other interventions during the trial, but only on their initiative. The use of cointervention will be assessed by questionnaires at all time points.

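### The Discussion claims that the added value of blended care can be identified, but the trial randomises only the whole package against usual care

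*Protocol article*

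**What the plan says.** All references are to the protocol article.

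- **Design (Abstract, Methods).** "A parallel-group design will compare an intervention group with a waiting list control group". Controls "will receive care as usual for the duration of this study and will receive the online intervention afterward".
- **Intervention Procedure.** After baseline, intervention participants are told "they will be given access to the online CAG" in effect: they get the online programme, and all of them are also invited to two consultations with a GP or practice nurse. For controls, a message follows baseline, "asking them to log out and return only for the next measurement", and "participants in the control group will receive care as usual". Both groups may use other interventions on their own initiative.
- **Strengths and Limitations, Overview.** The trial is described as very similar to the earlier online-only research, "which allows the results to be compared and the added value of blended care to be identified". The next sentence says the blended format is meant to widen reach, "specifically targeting a population that would not access an online-only intervention on their own".
- **Statistical Methods, Overview (Bayes factor paragraph).** One planned comparison involves the hypothesis that the blended intervention has smaller effects than those found earlier for the online-only CAG.
- **Principal Findings, Overview.** If results resemble the earlier ones, "this would confirm that the online-only intervention has been appropriately adapted to the blended care context, maintaining its effectiveness".

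**The concern.** The added value of blended care over the online programme is the difference between CAG with consultations and CAG alone. That contrast needs people who receive CAG alone, and no arm of this trial supplies them during follow-up. The two components always occur together in one arm, so randomisation identifies their joint effect against usual care and nothing finer.

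The statement in Strengths and Limitations therefore credits the study with a property that the design lacks. It also reaches the analysis, because the Bayes factor paragraph makes the comparison with the earlier online-only effects a planned result. A reported finding that blended care does better, worse or no differently than online-only could then be read as evidence about the consultations, whose time is one of the costed components in the Economic Evaluation. It would not be randomised evidence.

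**Working it through.** **1. What each source estimates.**

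| Source | Contrast | Randomised here? |
|---|---|---|
| This trial | online CAG + two consultations versus usual care | yes, by practice |
| Earlier online-only research | online CAG versus that research's own comparator | no, historical |
| Added value of blended care | online CAG + two consultations versus online CAG | no arm supplies it |

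Write P for the package effect in this trial's population, O for the online-only effect in this same population, and O* for the online-only effect found earlier. The added value is P − O. The planned comparison gives P − O*, and

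P − O* = (P − O) + (O − O*).

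The last term is the difference in online-only effect between the two study settings. This trial has no information on O, so the term cannot be estimated or removed. If the people reached here respond less to the online part than the earlier participants did, the term is negative and can hide a real benefit of the consultations. If they respond more, it can imitate one. Similar results are equally ambiguous. This holds however the hypotheses in the Bayes factor paragraph are paired.

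**2. Is there reason to set O − O* to zero?** The article asserts similarity and then, in the next sentence, states an aim of reaching people who would not take up an online-only programme unaided. It offers nothing else that fixes the term at zero.

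**3. Can other planned analyses fill the gap?** Statistical Methods allows subanalyses by degree of participation. Participation is chosen after randomisation, so these do not give a randomised component contrast either.

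**4. Precision, as illustration only.** The article gives no figure for added value, so there is none to reproduce. Inputs from Sample Size: 282 analysed (141 per arm, taken as stated), intracluster correlation 0.03, about 10 participants per practice. The stated design effect reproduces: 1 + (10 − 1) × 0.03 = 1.27.

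- Standard error of the standardised effect, unadjusted: √(2 × 1.27 / 141) = 0.134. The 95% half-width is 1.96 × 0.134 = 0.26.
- With residual change scores and an assumed baseline correlation of 0.6, the factor is √(1 − 0.6²) = 0.8, giving 0.26 × 0.8 = 0.21. For correlations from 0 to 0.6 the range is 0.26 to 0.21.
- At the 127 participants in 26 practices reported for December 2024 (4.88 per practice, equal arms, no dropout): design effect 1 + 3.88 × 0.03 = 1.117; standard error √(2 × 1.117 / 63.5) = 0.188; half-width 0.37, or 0.29 with the 0.8 factor.
- These describe P alone. The uncertainty of O* comes on top, and the article does not give it. If the earlier estimate came from 250 to 600 individually randomised participants (an assumption), its standard error would be 2/√250 = 0.126 to 2/√600 = 0.082. At 282, the half-width of P − O* would then be 1.96 × √(0.134² + 0.126²) = 0.36 down to 1.96 × √(0.134² + 0.082²) = 0.31. With the 0.8 factor in both studies it would be 0.29 down to 0.25.

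None of these figures includes the bias term O − O*.

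**The case against.** The strongest reply is that the article never claims a randomised comparison of blended with online-only care. It refers openly to previous research, its objective and design sections describe blended care against a waiting list with usual care, and the Bayes analyses are presented as complementary. All of that is correct, and it confines the fault to a claim in the Discussion and the matching Bayes comparison. It does not rescue the claim: to say that added value can be *identified* is too strong for a cross-study comparison.

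Several stronger readings are tempting, and the documents do not support them.

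- *The package is tested against nothing.* Controls receive usual care and may seek other help.
- *The two populations are known to differ.* The targeting sentence states an aim. The eligibility criteria in Recruitment of Participants do not exclude people who would use an online-only programme; they require internet access, some experience of it, and a device. The article does not describe the recruitment, unit of randomisation or setting of the earlier studies. What stands is that comparability is asserted, and that the article's own aim counts against it.
- *The added value is at most 0.20.* Sample Size gives an earlier range of 0.20 to 0.40 across lifestyle behaviours and a planning value of 0.40 at 6 months. Subtracting one from the other is the reader's inference; no expected increment is stated.
- *The Bayes factor treats the earlier effect as a fixed value.* The article does not say so, and a statistical analysis plan may settle it.
- *The sentence in Principal Findings makes the same error.* It is conditional and mainly concerns whether the package keeps its effect, which the comparison with usual care does address. *Confirm* is a strong word there, but that is a lesser matter.

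**Conclusion.** The point holds in limited form. The trial can estimate the effect of the blended package against usual care. It cannot separate the consultations from the online CAG, so it cannot identify the added value of blended care as the Discussion says. The conclusion follows from the composition of the two arms and needs no numerical assumption.

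The figures only show that the indirect comparison would also be imprecise. This trial's own half-width at the planned size is about 0.26 unadjusted, or 0.21 with an assumed baseline correlation of 0.6, before the earlier studies' uncertainty. Whether that is too wide for the increment of interest cannot be said, because the article does not state one.

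A reader might infer that the trial's main result is compromised. It is not: the randomised comparison, its outcomes and the multilevel analysis against usual care are untouched.

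**What to change.** 1. In Strengths and Limitations, replace the claim with wording such as: the trial estimates the effect of the complete blended package compared with usual care; it cannot isolate the contribution of the consultations, and any comparison with the earlier online-only studies is indirect.
2. In the Bayes factor paragraph, label the comparison with online-only CAG as indirect and exploratory, and state that the uncertainty of the earlier estimates is carried into it.
3. Optionally, in Principal Findings, soften *confirm* to *be consistent with*.

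The cost is small: wording, plus the earlier estimates' standard errors as an input to one supplementary analysis. No new arm, participants or data are needed, and analysis was to begin only once data collection ended. The downside is that the comparison with online-only CAG becomes less decisive.

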#### Future Directions

Future research could further investigate the implementation of eHealth for survivors of cancer in general practice or, depending on the results of this study, in different practice contexts. Emphasis should be placed on reaching survivors who are at risk of developing comorbidities or recurrence, or who have a high burden of disease that translates into medical costs or loss of productivity.

#### Dissemination of Research Findings

Research findings will be discussed with the consortium partners and published in academic journals. This study is the next step in disseminating the CAG in a practical context. However, to translate our findings to the real world, further research should be conducted to investigate how the intervention is sustained outside of the research protocol. Depending on our findings, the RCT will be followed by an implementation study in which survivors, GPs, and other stakeholders will be invited to share their views on the integration of blended CAG into regular cancer care.

#### Implications and Relevance

The number of survivors of cancer is expected to increase in the coming decades [2]. These survivors consult their GP with issues related to cancer survivorship, resulting in a high demand for general practice [19]. To support survivors of cancer in maintaining a healthy lifestyle and managing psychosocial needs, the online CAG program was developed [57]. The program was shown to be effective in promoting healthy lifestyle behaviors and reducing fatigue, depression, and anxiety [8-11]. Structurally embedding the CAG in general practice could support GPs and PNs in caring for their patients and help reach more survivors who need support after treatment. The expected ESs are small but arguably clinically relevant given the affordability, minimal associated risks, and widespread implementability of the blended CAG intervention [58,59]. The results of this study may have implications for cancer aftercare and general practice, and may also be relevant to the wider field of eHealth implementation.

### Conclusion

The research described in this study protocol will investigate the effectiveness (and cost-effectiveness) of a blended care intervention for survivors of cancer in general practice. The blended care intervention combines the use of a proven effective eHealth program (CAG) with face-to-face consultations with a GP or PN. Integrating eHealth for cancer aftercare into general practice may help GPs and PNs in caring for the growing number of survivors of cancer and may effectively improve their QoL, leading to reduced care needs in the future. The results of this study may be relevant to the field of cancer aftercare and general practice and will add to the literature on eHealth implementation.

## Appendix

Multimedia Appendix 1 Informed consent form.

Multimedia Appendix 2 Example of the Module Referral Advice (MRA).

Multimedia Appendix 3 SPIRIT checklist. SPIRIT: Standard Protocol Items: Recommendations for Interventional Trials.

## Abbreviations

CAG: Cancer Aftercare Guide
ES: effect size
GP: general practitioner
GPC: general practice center
GPP: general practice personnel
ISRCTN: International Standard Randomised Controlled Trial Number
ITT: intention-to-treat
METC Z: Medical Research Ethics Committee of Zuyderland hospital and Zuyd University of Applied Sciences (medisch-ethische toetsingscommissie van Zuyderland en Zuyd Hogeschool)
MRA: Module Referral Advice
PA: physical activity
PN: practice nurse
QALY: quality-adjusted life year
QoL: quality of life
RCT: randomized controlled trial
